### Outcomes

Primary outcome: incidence of pressure ulcers by ICU are obtained from the total of PU-bearing individuals, developed during the period of the study in each ICU by each group of clusters. The number of bedsores (Grade I –grade IV) is newly acquired after admission into ICU for 1000 days.

Secondary outcomes: risk of PU (hazard ratio, HR) and time to event individually in patients assigned to the intervention group and the active control group, taking into account the first event of each patient. Also, we will include safety results such as complications due to postural changes (permanent or sporadic shifts in ventilation measures, hypoxemia, hemodynamic changes like, for example, tachycardia or hypertension; events such as severe respiratory insufficiency; cardiogenic shock, pneumonia, or death).

### Classification of pressure ulcers

Pressure Ulcers would be classified as grade I to IV according to The Pressure Ulcer Advisory Panel Consensus Development Conference [21] (NPUAP) 1989, and the National group for the study and counseling in Pressure Ulcers and Chronic Wound-Spain [22] (GNEAUP), 2003. We did not use the new pressure ulcer terminology (pressure injury) and the updated stages provided by The National Pressure Ulcer Advisory Panel- NPUAP, given that all hospitals in our country follow the Ministry of Health Guidelines according to the primary pressure ulcers classification and also Pus are reported in this way.

This system, accepted until very recently, establishes four stages for pressure ulcers. The main objective of any classification system is to standardize the collection of information and provide a standard description of the severity of the ulcer for both clinical practice, evaluation, or research purposes.

This classification defines ulcers from grade I to grade IV. Grade I describes an ulcer with erythema that does not pale on intact skin. Edema, induration, discoloration, and local heat are seen in dark-skinned patients. Stage II is described as a partial skin loss that affects the epidermis, dermis, or both. It is classified as a superficial ulcer with the appearance of abrasion, blister, or shallow crater. Grade III ulcer is described as a total loss of skin thickness that involves injury or necrosis of the subcutaneous tissue, which may extend downward but not through the underlying fascia. Stage IV is considered the total loss of thickness with extensive destruction, tissue necrosis, or injury to muscle, bone, or supporting structure. In this stage, lesions such as caverns, tunnels, or winding paths can occur. This classification is the currently way each hospital has to report PU to the Ministry of Health and Social Protection in Colombia.

### Data collection and procedure

Various hospitals from different regions of Colombia will be recruited from a list of 60–100, each of which will be handed a feasibility survey and a prior discussion, which will help decide each hospital’s eligibility for entering the study. Any hospital that decides that the study is allowed to proceed in its facilities (depending on board matters, nurse-patient relationship, and prior consent to execute interventions resulting from randomization, approval from the medical director and nursing director with a prior protocol explanation) agrees and commits to participating in the study and executing the designated intervention. Having decided which hospitals are eligible, the study will be sent to their own board of ethics committees for careful evaluation and approval.

If this is the case and to proceed with the study, the medical director and nursing director must sign a consent form and all involved nursing staff based on the hospitals’ ethics committee demands. Patients will also be required to sign a document of informed consent to authorize the registration of relevant data regarding their health and medical record. Once each hospital is familiar with the assigned intervention**,** all involved staff will receive instructions for the study implementation and its procedures to be applied in their respective ICUs.

Each intervention will be executed by healthcare staff (nurses and nursing assistants) consecutively according to the allocated intervention in all patients until reaching the study sample in each ICU (150 patients). For ensuring the consistency of the interventions, the total of postural shifts per ICU, in all frequencies, will be recorded daily during a span of 3 months along the course of the intervention by a data collector from patient’s charts from both groups.

A patient will remain in the study from the moment of admission into the ICU until he or she is either transferred to another service or another hospital center, begins walking, or ambulation develops a pressure ulcer or dies.

Each center will designate a leader responsible for the PENFUP phase 2 study procedures in each ICU. Each leader must ensure the complete execution of the project day by day and the accurate application of the assigned intervention in each shift. The healthcare staff assigned to group A (high frequency each 2/ h) will receive automatic text messages by cellphone twice a week to remind the intervention frequency to be applied. Leaders from each center will designate two groups of data collectors to operate based on the informed consent given by patients or their families and will gather information of each intervention day bay day in a register format to be completely archived into the study’s platform, including the number of total daily posture shifts per patient in each ICU.

Each center will receive a set of general initiation instructions in person or via teleconference or internet conference. Each center will also receive the investigators’ manual and questionnaires for collecting data to be included in the study’s platform. The total of postural shifts in 24 h will be registered to maintain proper management of the number of shifts per patient calculated for both high and conventional care. Other variables that will be included contain information of each hospital (the type of hospital, total number of nurses, relation nurse-patients, type of prevention protocols for pressure ulcers, and incidence of a pressure ulcer from the year before the beginning of the study); and patient variables (demographic, health history, health status in ICU, complications in ICU, pressure ulcers and location, repositioning complications and reason of ICU discharge) (Table 1).

**Table 1 Tab1:** Variables and timeline for inclusion by each ICU. The complete timeline for each ICU is about 3–4 months

Variables and time to collection 1–4 Months by ICU	Variable to be obtained in each ICU				Type of variable by ICU by Intervention and Control			
**Months 1 to 4**	**T1√**	**T2√**	**T3√**	**T4√**	**T1√**	**T2√**	**T3√**	**T4√**
**1-Primary Outcome**	Development of new pressure ulcers in clusters: ▪ Areas defined of injury: sacrum, heels, ankles, elbows, hip, scapula ▪ Others				Rate ulcers per ICU /total control Rate ulcers per ICU/total intervention Median (IQR).			
	Stage of ulcers: I, II, III, IV + o Indeterminate				Total ulcers per stage per ICU per group /150 patients N (%) by cluster			
**1–4 Months by ICU**	**T1√**	**T2√**	**T3√**	**T4√**	**T1√**	**T2√**	**T3√**	**T4√**
**2-Secondary Outcome**	Complications during repositioning				Categorical: Hemodynamic changes, Respiratory Changes, ventilator changes, others.			
	Risk of PU in individuals				Hazard ratio (HR) Date of appearance of the PU (day-month-year) Time to the event (survival analysis)			
**1–4 Months by ICU**	**T1√**	**T2**	**T3**	**T4**	**T1√**	**T2**	**T3**	**T4**
**Variables to be controlled as possible confusion variables**	Old PUs identified upon entry to ICU (presents at the baseline). ▪ Other injuries such as burns, mask injuries, tube injuries, surgical wound dressings In ICU, PUs or dressing site (foam, hydrocolloid)				Total of patients with PUs up-to-baseline/150 patients by cluster (variable to be controlled) N(%)			
**1–4 Months by ICU**	**T1√**	**T2**	**T3**	**T4**	**T1√**	**T2**	**T3**	**T4**
**3-Characteristics of patients [demographic, Health status,**	Age (years), sex (M, F)				Mean (SD), N(%)			
	Body Mass Index (BMI)				Median (interquartile range) or mean (SD)			
	Patients´ Weight at admission				Median (interquartile range, IQR) or mean (SD)			
	Patients´ Height at admission				Median (interquartile range, IQR) or mean (SD)			
	Type of comorbidity to patient admission: Cardiovascular condition, Respiratory condition, Diabetes, Neurological, Malignancy of Carcinoma, Kidney Disease, Peripheral Vascular Disease, Cerebrovascular Accident, Transplant, dermatitis o eczema, documented malnutrition on admission, others.				N(%)			
	Length of hospital stay in ICU (Hours, days) (admission to ICU-Discharge from ICU)				Date: day/month/year Median (interquartile range, IQR) or mean (SD)			
	Patient-days involved in the study (by cluster and				Median (interquartile range, IQR) or mean (SD)			
**1–4 Months by ICU**	**T1√**	**T2√**	**T3√**	**T4√**	**T1√**	**T2√**	**T3√**	**T4√**
**4-Complications of patients in ICU**	Cardiovascular, neurological, sepsis, respiratory, delirium, TEP, musculoskeletal, shock, death				N(%)			
**4-Dates of the possible end of the following in ICU**	First ambulation in ICU Transference to hospital service Hospital transference Death				Day/Month/Year			
**1–4 Months by ICU**	**T1√**	**T2**	**T3**	**T4**	**T1√**	**T2**	**T3**	**T4**
**5-Characteristics of the cluster (or ICU)**	Type of hospital: Public, Private, University, other				N (%)			
	Skin Care Group Preventive care use-report on medical history				N (%)			
	Care guide or policy Institutional Preventive (Yes-No) Name of guideline				N (%)			
	Professional Nurses per shift				Median ó mean (interquartile range IQR)			
	Auxiliares per shift				Median ó mean (interquartile range, IQR)			
**1–4 Months by ICU**	**T1√**	**T2√**	**T3√**	**T4√**	**T1√**	**T2√**	**T3√**	**T4√**
**6-Intervention Characteristic**	Adherence in ICU to intervention				Compliance day by day (yes = 1, no = 2) % compliance (calculated from 80% days stay per patient) ▪ Number of times one patient is mobilized in the intervention ▪ Description of the teams (total number of people who mobilized the patient) ▪ Total number of teams repeating intervention per shift ▪ The number of head and auxiliary nurses per team.			
	Acceptance of the final intervention of the study				Evaluation of the acceptability of the intervention by the personnel			
	Description of usual or conventional care by ICU				Descriptive Individual __or group__ Frequency per shift__ Position variation: yes_ No_ Descriptive.			

If by any chance (including medical assessment or clinical practice setbacks), patient mobilization is decided to be avoided, patients will be excluded from adherence to the intervention (temporarily or definitely), given the pragmatic nature of the study. This information will be registered on the platform. Regular follow-up will be ensured to verify if data is submitted completely and coherently. This will be done by the platform coordinator of PENFUP phase 2. When a pressure ulcer is detected, the nurse in charge of each patient will report it in the individual medical record and will assess the depth of each wound (Fig. 2. SPIRIT figure of study timeline).

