### Randomization and blinding

Previous consent to participate will be solicited for the director of each cluster (medical director of the ICU, nursing coordinator of the ICU) and for nursing staff that will perform the intervention.

All the ICUs participants will be randomized (ratio 1:1) to be assigned to either an intervention group (an indication of repositioning every 2 h) or to conventional care (Intervention provided by care providers using a non-standardized frequency of repositioning). The randomization will be set in the main execution center of the study, which is Fundación Cardioinfantil located in Bogotá, and will be computerized with random numbers. Besides, randomization will be executed using a permutation design by blocks of two possible combinations (intervention A or B). The allocation will be openly announced in each hospital. The study will be blind to evaluators (internal analysts and statisticians) [16, 19, 20]. Furthermore, following this, we plan to apply a consent form for the patients [or their parents according to their health status] when admitted to the ICU.

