### Design of Intervention

#### Intervention group a (frequent repositioning ≤ to every 2 h)

The intervention group received a repositioning with a frequency interval which we call “high-frequency” to be applied to every admitted patient consecutively, at a level that is lesser than or equal to every 2 h in a 24/h span (this is with a minimum goal of 8–12 position shifts in 24 h minus 2 o 3 at night to prevent altering the patients’ circadian rhythm). Changes in position will be executed so that patients go from a lateral-right position to a supine position, and later a lateral-left position; or from a lateral-right position to a lateral-left position or vice versa; or from a supine position to a prone position or vice versa [only if this repositioning is provided every 2 h]. The supine position can be overlooked as long as the postural shift is made at the indicated time.

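### No skin-inspection schedule common to both arms is stated, so the primary rate ratio is open to detection that differs with turning frequency; the net direction is unknown

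*Protocol article*

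**What the plan says.** All references are to the protocol article.

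- **Ascertainment.** Data collection and procedure, after Table 1: "When a pressure ulcer is detected, the nurse in charge of each patient will report it in the individual medical record", and this nurse also assesses the depth of the wound. The shown text gives no inspection times.
- **Follow-up.** The same section begins "A patient will remain in the study from the moment of admission into the ICU until he or she is either transferred" and lists the other end points: walking, an ulcer, or death. The control-group section likewise ends follow-up at the first stage I ulcer. Neither mentions a skin check on leaving the ICU.
- **Turning, arm A.** "at a level that is lesser than or equal to every 2 h in a 24/h span". The daily target is 8 to 12 turns, with fewer at night.
- **Turning, arm B.** Usual care, with no frequency fixed. The hypothesis in the Background puts conventional turning at 4 h intervals or longer.
- **Endpoint.** Outcomes counts grades I to IV. Under Classification of pressure ulcers: "Grade I describes an ulcer with erythema that does not pale on intact skin".
- **Patients and sites.** Eligible patients cannot move themselves. Table 1 lists sacrum, heels, ankles, elbows, hip, scapula and others.
- **Who knows the allocation.** "The allocation will be openly announced in each hospital". The turns are done by ICU nurses and nursing assistants. Only analysts and statisticians are blind, although the Background calls the trial double-blind.

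**The concern.** An ulcer enters the primary numerator only once a nurse has seen it. In a patient who cannot move, skin over the sacrum, hip or scapula is hidden in some positions and comes into view at a turn. With no separate inspection schedule, the chance to see a lesion plausibly follows the number of turns, and that number is what the trial randomizes. Grade I erythema on intact skin is the stage most easily missed, or gone by the next look.

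The primary analysis divides arm A's rate by arm B's, so any ratio of detection probabilities multiplies straight into the result. Earlier detection in arm A would also bring forward its event times in the Cox model and make its lesions look milder in the planned comparison of stages. A true benefit could be diluted. This would occur even with perfectly honest assessors, and blinding the analysts does not touch it.

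**Working it through.** The plan gives no figure for detection, so there is none to reproduce on this point. The calculations below show only how large the effect could be.

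**1. Inputs.** Arm A interval T = 2 h (stated); 8 turns a day, the lower end of the stated goal, averages 24/8 = 3 h. Control T = 4 h (edge of the hypothesis) and 6 h (the Background cites 4 turns in 24 h as a low rate; 24/4 = 6). Assumptions not in the documents: each turn is one look, every look detects a visible lesion, and visible erythema lasts an exponential time with mean D = 6, 12 or 24 h.

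**2. Lesions that fade.** With onset uniform between turns, P(seen) = (D/T) × (1 − exp(−T/D)). For D = 6 h and T = 2 h: 3 × (1 − 0.7165) = 0.850.

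| D | T = 2 h | T = 3 h | T = 4 h | T = 6 h | 2 v 4 h | 2 v 6 h | 3 v 4 h |
|---|---|---|---|---|---|---|---|
| 6 h | 0.850 | 0.787 | 0.730 | 0.632 | 1.17 | 1.35 | 1.08 |
| 12 h | 0.921 | 0.885 | 0.850 | 0.787 | 1.08 | 1.17 | 1.04 |
| 24 h | 0.959 | 0.940 | 0.921 | 0.885 | 1.04 | 1.08 | 1.02 |

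The last three columns are the observed rate ratio when the true ratio is 1. A true ratio of 0.50 would be observed as 0.50 × 1.04 = 0.52 up to 0.50 × 1.35 = 0.67 for a 2 h interval in arm A.

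**3. Lesions that persist until seen.** Only exit before the next look hides a lesion, so the same formula applies with D replaced by the ICU stay. For an assumed mean stay of 8 days (192 h), P(seen) is 0.9948, 0.9897, 0.9845 and 0.9694 at T = 2, 4, 6 and 12 h. The ratios of the 2 h value to the others are 1.005, 1.010 and 1.026. A simulation with the same stay and about 7.5% control incidence gave 1.003, 1.008 and 1.025. If each look finds only half of the lesions present, the simulated values rise to 1.01, 1.03 and 1.09.

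**4. The opposite mechanism.** If arm A staff, who know the allocation, leave a fraction f of ulcers unreported, the observed ratio at a true ratio of 1 is 1 − f: 0.90, 0.80 or 0.70 for f = 10%, 20% or 30%. Under-reporting of 1 − 1/1.04 = 4% would cancel the smallest detection ratio for 2 h turning, and 1 − 1/1.35 = 26% the largest.

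**5. Could detection alone produce a significant result?** Take 11 ICUs of 150 per arm (1,650 patients), ICC 0.035 and control incidence 0.075. The design effect is 1 + 149 × 0.035 = 6.215, so the effective size is 1,650/6.215 = 265.5 per arm. For a ratio of 1.35, arm A has 0.10125 and the difference is 0.02625. The standard error is √[(0.10125 × 0.89875 + 0.075 × 0.925)/265.5] = 0.0246, so z = 1.07. Ratios of 1.17 and 1.08 give z = 0.54 and 0.26.

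**The case against.** The strongest reply is that this argues from silence in a condensed article. The quoted sentence says who records an ulcer once found, not when skin is inspected. The investigators' manual, the data-collection questionnaires and the SPIRIT timeline figure are not shown and may contain a schedule. **This stands in part:** the point concerns the rule as stated, and if a schedule exists the remedy is to state it.

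Second, no sentence ties inspection to turning, ankles and elbows can be seen without a turn, and local prevention protocols continue in both arms. **This stands as a limit:** the link is plausible, not documented.

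Third, a reader might infer that the primary ratio is biased against the intervention. The documents do not support a signed claim. The staff group that delivers the turns knows the allocation and grades a subjective sign, which could push the ratio the other way by a similar amount. Less-turned patients might also keep erythema longer, which would offset the effect.

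Fourth, a reader might infer that unequal detection could halt the trial, because the Abstract makes a significantly worse result in the experimental group a reason to stop. With no true effect, even the largest ratio above gives an expected z of only about 1.1 at full sample, and less at the interim analyses, so this consequence is weak.

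Fifth, extra skin checks could add turns in the control arm and so change usual care. Counting only what a scheduled check finds would also change the endpoint and conflict with follow-up ending at the first stage I ulcer. Both objections stand and shape the fix. They do not remove the need for one.

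**Conclusion.** The point holds in a limited form. As the protocol article states it, detection of the primary outcome may depend on the arm, and the rate ratio and hazard ratio cannot separate prevention from detection. Taken alone, the mechanism works against the intervention; the net direction is unknown.

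The size rests on assumptions outside the documents. At a true ratio of 1 the observed ratio is about 1.00-1.03 if lesions persist, every look detects and control is turned every 4-12 h. It is about 1.04-1.35 if every event is erythema fading with a mean of 6-24 h and turning is every 2 h against every 4-6 h. It drops to 1.02-1.08 if arm A averages 3 h against 4 h. The endpoint mixes grades I to IV, so the fading figures lean high on that count; looks that miss lesions would raise both ranges.

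This is worth correcting before recruitment because analysis cannot repair it. Follow-up ends at the first stage I ulcer, so restricting to grade II or higher would lose the lesions caught early, and would lose more of them in whichever arm is looked at more often.

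**What to change.** - State that the primary outcome comes from a skin check at the same scheduled times in both arms, for example once per nursing shift, and at ICU exit. Do each check at a turn already due, so that usual-care turning is unchanged.
- Record each check in the daily register that data collectors already complete, and date the first ulcer by that check.
- Align the two end-of-follow-up statements (control-group section; Data collection and procedure) with this, so that follow-up for the primary outcome ends at the first ulcer found at a scheduled check.
- List ulcers noted only between checks separately, and include them in a sensitivity analysis.
- If the investigators' manual already sets a common schedule, state it in the protocol instead.

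The cost is protocol wording, one register line and a few minutes of existing nursing time per check. Slightly fewer transient grade I events will count, and the sensitivity analysis shows how much that matters. The change evens out the opportunity to detect an ulcer. It does not blind the nurses, so reporting bias from known allocation remains.

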### Statistical analysis

All ICUs shall be analyzed according to the branch they were randomized to (Intention to treat) [7, 23]. The incidence of PU will be analyzed considering the time of natural first appearance; that is, within the time-lapse in which the patients are in the study. The two-time variables to be considered for this analysis will be admission into the ICU and the emergence of PUs since the time of admission for each patient. Also, we will include the length of stay in the ICU. The characteristics of the clusters and each individual will be analyzed considering counts (%), means (SD), medians (interquartile range). The percentage of applied interventions (repositioning) by clusters in each group will be computed according to the total of interventions that should be administered in both branches of high frequency and conventional care. The primary analysis will be done at the cluster level (ICU) and the secondary at an individual level (each patient). When analyzing at a cluster level, the total number of PUs will be divided by the total of accumulated days of each patient in each cluster to obtain incidence rates in both groups; this is done based on the permanence of the patients from each cluster. To calculate the incidence rate (IR of 95%), the incidence rate in the groups with a higher frequency of postural changes in group A will be divided by the control groups’ incidence rate of postural changes in group B. The incidence of PU will be analyzed considering the time of natural first appearance; that is, within the time-lapse in which the patients are in the study.

The secondary result includes evaluating the frequency of the severity of PUs (stages I - IV) and will be compared with both groups using an adjusted Chi-square test. For the individual evaluation of the risk of PUs in patients, the first PU to appear in each patient will be considered for calculating the rate of events and time before the event. The hazard ratio (HR) will be computed using Cox proportional-hazard models and its corresponding 95% confidence intervals (CI), adjusted by the standard error by cluster (SE) [23]. The Cox models will be implemented for exploring relations between the main result and the explanatory considering the time before the time of occurrence.

The Hazard Ratio is an estimate that derives from the Cox model, and this is from the rate of risk index between the groups that received a higher frequency rate of postural changes than the groups that received conventional care of postural changes. An adjusted analysis by co-variables will be developed considering the related risk factors in the literature for developing PUs (age and comorbidity). The safety outcomes will be described as the registered events regarding posture shifts in each branch according to their frequency level in interventions A or B, and the association between posture shifts and their compilations will be explored. To detect early differences in the occurrence of events amongst the groups, we planned two interim analyses; once the 33 and 66% of the units are randomized, these internal analyses will be made using the sequential method [23].

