### Sample size

Twenty-two ICUs will be included, each with a total of 150 patients in each branch of the study until completing a sample size of 3.300 patients. The calculation for this sample considered the rate of pressure ulcers observed in PENFUP phase 1 (7.5%) in the control group (patients who received preventative care with skin moisturizing) [17]. As a result of this process, it was decided that the highest incidence rate acceptable for the conventional group for repositioning would be 0.075 and that the incidence in the intervention group with high repositioning frequency would be 0.023 (2.3/7 = 0.32).

For the hypothesis of the study, we calculated a 50% low-impact reduction in pressure ulcers in ICUs that execute repositioning at a high frequency (intervention group A), compared to the ones that implement repositioning at conventional care or control group. The number of ICUs and individuals in there would be obtained by a calculation considering an intra-class correlation coefficient of 0.035 previously attained in the Chaboyer study et al. (2016), a power of 80%, and an alpha error of 0.05% resulting in a 50% difference between both intervention groups [18].

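### The primary rate ratio should be tied to the 22 ICU rates rather than left open to pooled arm totals, and the collected prior-year ulcer incidence should be used as a cluster-level covariate

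*Protocol article*

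**What the plan says.** All of this is in the protocol article.

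- **Primary contrast.** The Statistical analysis section puts the primary analysis at the level of the ICU and the secondary analysis at the level of the patient. Ulcers are divided by the patient-days accumulated in each cluster to give rates in the two groups, and then "the incidence rate in the groups with a higher frequency of postural changes in group A will be divided by the control" group's rate. A 95% label is attached, but no test, model or variance for the ratio is named.
- **Display.** Table 1 lists the primary outcome as a rate per ICU, by arm, with median and interquartile range.
- **Secondary analyses.** The Cox hazard ratio has its standard error adjusted by cluster, and severity is compared with an adjusted chi-square test.
- **Covariates.** "An adjusted analysis by co-variables will be developed considering the related risk factors in the literature for developing PUs (age and comorbidity"). Table 1 adds, as variables to be controlled, old ulcers at ICU entry and other injuries or dressings.
- **Baseline of the outcome.** Among the hospital variables, the Data collection and procedure section lists the "incidence of a pressure ulcer from the year before the beginning of the study". No analysis is said to use it.
- **Design.** "Twenty-two ICUs will be included, each with a total of 150 patients"; "All the ICUs participants will be randomized (ratio 1:1"). The sample size uses an intra-class correlation of 0.035. ICUs of one hospital receive the same allocation (Inclusion and exclusion criteria).

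**The concern.** The only primary contrast written down is one group's rate over the other's. That sentence fits two different analyses. One compares 22 ICU rates and carries the variation between ICUs. The other adds up ulcers and days within each arm and puts an interval on two totals, which treats 3,300 patients as independent. The section says how clustering enters the secondary hazard ratio but does not say so for the primary ratio.

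The error rate of the main test is at stake. According to the Abstract, a difference below 0.05 in the main outcome also decides whether the trial stops, so the ambiguity reaches the two interim analyses.

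The second part concerns efficiency. With few clusters, most of the variance lies between ICUs. A baseline measure of the outcome at that level is the kind of covariate that can reduce it, and the trial already collects one.

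**Working it through.** **Inputs from the article.** 22 ICUs, 150 patients each, 3,300 in total; 1:1 allocation, so 11 ICUs and 1,650 patients per arm; incidence 0.075 versus 0.023; intra-class correlation 0.035; power 80%; alpha read as 0.05, two-sided.

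**1. Reproduce the sample size.**
- Two proportions, 0.075 versus 0.023: 270 patients per arm.
- Design effect = 1 + (150 − 1) × 0.035 = 6.215.
- 270 × 6.215 = 1,678 per arm, or 11.2 ICUs per arm and 3,356 in total. This is within 3% of the stated 3,300.
- Power at 1,650 per arm is 79.4%.

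The design therefore counts on between-ICU variance. (A 50% reduction, 0.075 versus 0.0375, does not reproduce 3,300. That is a separate matter, so 0.075 versus 0.023 is the base case for power below.)

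**2. If arm totals were pooled.**
- The standard error is too small by √6.215 = 2.49. Measured against a Poisson standard error at a ratio of 0.50, the factor is 0.378 / 0.156 = 2.4.
- Analytic type I error = 2 × [1 − Φ(1.96 / 2.49)] = 43%.
- Simulation (beta-binomial, 11 ICUs of 150 per arm, 7.5% in both arms, equal follow-up, 40,000 runs): 41% for the pooled Poisson log ratio, against about 5% for a t-test on the 22 ICU rates with 20 df.
- At an assumed lower correlation of 0.005 or 0.01, the pooled error is still 12% or 20%.

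| Rate ratio | 95% CI, pooled Poisson | 95% CI, with between-ICU variance (t, 20 df) |
|---|---|---|
| 0.50 | 0.37–0.68 | 0.23–1.10 |
| 0.307 | 0.21–0.44 | 0.12–0.79 |

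At a ratio of 0.50 the two readings lead to opposite conclusions.

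**3. What prior-year incidence could add.** The design effect splits into a within-ICU part, 1 − 0.035 = 0.965, and a between-ICU part, 150 × 0.035 = 5.25. A cluster covariate with correlation r to the underlying ICU rates leaves 0.965 + 5.25 × (1 − r²). The article gives no r, so the values below are assumed.

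| r | Design effect | SE reduction | Power, 0.075 vs 0.023 |
|---|---|---|---|
| 0 | 6.215 | – | 79% |
| 0.3 | 5.74 | 4% | 82% |
| 0.5 | 4.90 | 11% | 88% |
| 0.7 | 3.64 | 23% | 95% |

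These powers are before the loss of one degree of freedom.

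**4. A remedy to avoid.** One tempting ICU-level method adds 0.5 to each count, takes logs, compares arms and exponentiates. Simulated under the same set-up with the correlation at 0.035 in both arms, it centres on 0.42 when the true ratio is 0.50, and on 0.24 when it is 0.307. Coverage of the true ratio is 93% and 91%. About 14% and 30% of intervention ICUs have no events.

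**The case against.** A reader might infer that the plan ignores variation between ICUs and that its interval is therefore too narrow. The text does not support that. It says that the primary analysis is at cluster level, it accumulates days in each cluster, and Table 1 summarises rates across ICUs. A comparison of those rates carries the between-ICU variance. The sample size allows for clustering and so does the Cox model, which makes a deliberate pooled analysis less likely. The interval method is also largely a detail that a condensed article leaves to the analysis plan, which is not shown. This stands, so the 41% is a conditional figure. What remains is that the contrast as written permits the invalid reading, and the median and interquartile range are descriptive only.

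A reader might also infer that leaving out prior-year incidence is an error, or that precision is certainly lost. Neither follows. An unadjusted randomised comparison is valid. The item is recorded per hospital, over a population that may differ from the immobile patients with intact skin enrolled here, so it may predict ICU rates poorly. Nor is adjustment confined to age and comorbidity, because Table 1 names further variables to be controlled. The covariate is a recommended improvement and no more than that.

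**Conclusion.** The point holds as a request to fix an ambiguous primary contrast, together with a low-cost gain in precision. It does not hold as a finding that the planned interval is wrong. Pooling with a Poisson-type interval would give a type I error of about 41% at the trial's own correlation; comparing ICU rates would give about 5%. These figures assume equal cluster sizes, equal follow-up per patient, and that the correlation for a binary risk carries over to the rate. Independent units may number fewer than 22, because ICUs of one hospital share an allocation.

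The benefit of prior-year incidence is 4% to 23% of the standard error over an assumed r of 0.3 to 0.7. The documents give no value for r.

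**What to change.** - **Primary method.** State that the rate ratio is estimated from ICU-level data with between-ICU variance. Two examples are a count model with log patient-days as offset and a cluster-robust standard error corrected for few clusters, or a t-based comparison of ICU rates. With 22 independent units this has about 20 degrees of freedom, or 19 with one covariate.
- **Unit.** Use the hospital as the unit wherever several of its ICUs share an allocation.
- **Covariate.** Prespecify prior-year ulcer incidence as a cluster-level covariate, in a form that is defined when a hospital reports zero. A plain logarithm is not.
- **Avoid.** Do not report the exponentiated difference of log(count + 0.5) rates as the rate ratio, because it exaggerates the effect.

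**Cost.** A change to the analysis text and one degree of freedom out of about 20. The article already lists prior-year incidence for collection, so no new data or patients are needed. The gain will be small if hospital-level prior incidence predicts ICU rates poorly.
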